**Translation of the approved study protocol (only methods section in agreement with editor)**

**Methods:**

*Design and recruiting:* The study is a randomized multicenter trial with 6 month follow-up with the participation of Regionalhospitals Silkeborg, Viborg, Horsens, Herning, and Aalborg University Hospital. A total of 140 patients with medically treated lung embolism (LE) will be included in the study, 70 in each group (Figure 1). The inclusion criteria are as follows: 1) objectively verified acute PE (ICD10 I260 and ICD10= I269); including recurrent LE; 2) treatment of LE with anticoagulant drugs; 3) 18–80 years of age; and 4) competency in the Danish language. Patients will be excluded in the case of: 1) PE as a secondary finding in relation to a scan performed due to another disease; 2) severe co-morbidity (e.g., severe heart disease, severe, active cancer, severe psychiatric disease, e.g. schizophrenia or depression). The nurses or physiotherapists at the cardiac wards of the participating hospitals will perform daily screening of patients hospitalized at the ward with the aim to recruit eligible patients according to the above criteria. On the day of discharge eligible patients are informed about the study, and the written study information is handed out (Appendix 1). Patients have a right to two days of deliberation time, and will be contacted by telephone hereafter to ask for participation in the project. By acceptance of participation written consent is retrieved (appendix 2) when the patients arrive for their baseline test in the AK-clinic (anti-coagulation clinic) app. 14 days after discharge. Following the baseline tests, patients are randomized to either the control group or the intervention group using opaque, sealed envelopes. Block randomization by hospital is used to ensure that approximately an equal number of patients at each hospital will be allocated to the control- and the intervention group, respectively.

[Figure 1. Flowchart as in manuscript]

**Outcomes and methods of measurement:** Data on patient's age, sex, BMI, medical treatment of LE, diagnosis (cause of LE) are retrieved from medical records at baseline.

- Primary outcome: Change in physical capacity, measured with the Incremental Shuttle Walk Test (appendix 3) from baseline to 6 months follow-up.
- Secondary outcomes: Change from baseline to 6 months follow-up on the following parameters:
  - Disease-specific quality of life measured with the Pulmonary Embolism Quality of Life questionnaire
  - Generic quality of life measured with EuroQol-5 Dimensions
  - Sick leave (number of days in the past 4 weeks)
  - Use of painkillers and psychoactive drugs the past 4 weeks.

36  
37  
38  
39  
40  
41  
42  
43  
44  
45  
46  
47  
48  
49  
50  
51  
52  
53  
54  
55  
56  
57  
58  
59  
60  
61  
62  
63  
64  
65

The secondary outcome measures are collected in one questionnaire (appendix 4)  
The primary endpoint is 6 months after baseline test. In addition an intermediary measurement is performed 8 weeks after baseline (after termination of exercise program, see figure 1).

*The Incremental Shuttle Walk test (ISWT)* has been developed for assessing and measuring changes in a person's maximum walking capacity. The reliability and validity of the test has been shown in several studies and has been found acceptable. Studies show a reasonable association between maximal oxygen uptake and the ISWT, and that this association is better than the association between maximum oxygen uptake and the 6 minute walking test. The test has been validated within a number of study populations, including patients with heart and lung diseases [18].

The Pulmonary Embolism Quality-of-Life (PEmb-QoL) is a disease-specific quality of life questionnaire, containing six dimensions, covering frequency of complaints (8 items), activities of daily living (ADL) limitations (13 items), work-related problems (4 items), social limitations (1 item), intensity of complaints (2 items), and emotional complaints (10 items).

The EuroQol Five Dimensions (EQ-5D) is a generic quality of life questionnaire comprising both a descriptive part with 5 dimensions and the visual analogue scale EQ-VAS. The five dimensions mobility, self-care, usual activities, pain/discomfort, and anxiety/depression) [22, 23].

Sick leave and use of psychotropic drugs is gathered in questionnaires. Regarding sick leave the patient is asked to state the number of days' sick leave within the last four weeks according to the following categories: 0 work days; 1-4 days per week; 5-7 days per week. Regarding use of psychotropic drugs (e.g antidepressive medicine, anxiety reducing medication, sleeping pills) the patient is asked to state their average weekly use within the last four weeks according to the following categories: 0 days per week, 1-4 days per week, and 5-7 days per week.

The baseline measurements are performed by the physiotherapist who sees the patient at he baseline visit 14 days after their discharge. The following tests at 8 weeks and 6 months are performed by a project physiotherapist, who is blinded as to the patient's group allocation. When the patient is summoned for the follow-up tests it is underlined that the patients must not reveal their group allocation.

66      Tabel 1. Overview of measurement timepoints

| Timepoint      | Baseline
14 days after discharge | 1st follow-up
8 weeks after baseline | 2nd follow-up
6 months after baseline |
|----------------|-------------------------------------|-----------------------------------------|------------------------------------------|
| Outcome |                                     |                                         |                                          |
| Incr SWT       | X                                   | X                                       | X                                        |
| PEmb-QoL       | X                                   | X                                       | X                                        |
| EQ-5D          | X                                   | X                                       | X                                        |
| Sick leave     | X                                   | X                                       | X                                        |
| Medication     | X                                   | X                                       | X                                        |

67      *Incr SWT = Incremental Shuttle Walk Test; PEmb-QoL = Pulmonary Embolism Quality of Life*  
68      *Questionnaire; EQ-5D = EuroQol 5 Dimensions*

69

70      **Interventions**

71      *Group 1, usual care:* A usual course of treatment typically entails 3-5 days of hospitalization where  
72      anticoagulant treatment is initiated. The patient and his or her relatives receive general information  
73      about the disease and the course of treatment, the medication, and future prevention of embolism.  
74      Approximately 2 weeks after discharge the patient is seen at the hospital for control of their  
75      medication and the following outpatient visits are planned individually depending on the patient's  
76      needs. Any other treatment that may be offered at the hospitals, e.g. contact with physiotherapists  
77      during hospitalization can vary between hospitals. The patients are scheduled for physical tests and  
78      completion of questionnaires at 8 weeks and 6 months.

79      *Group 2, homebased exercise:* In addition to usual care, patients are offered participation in an  
80      eight-week home-based exercise program with telephone follow-ups after 1, 2 and 4 weeks.  
81      Following the completion of the baseline measurements the physiotherapist has a dialogue with the  
82      patient regarding the importance of exercise and how the patient can schedule the exercise in their  
83      everyday life. In brief, the patients are recommended to exercise for a minimum of three times per  
84      week for 1 hour, with intervals (20 minutes in total) at a high intensity level, where only very short  
85      sentences of speech are possible). The remaining 40 minutes are at a moderate intensity, where you  
86      are only slightly out of breath, but having a conversation is possible. The patients can choose  
87      whatever type of exercise they prefer, and they are generally encouraged to choose an exercise  
88      modality they already perform, or a modality they have previously had positive experiences with.  
89      The patients record all their training sessions in a diary handed out at the first visit (appendix 5).  
90      The training diary can be handed out in paper or be sent on email. The training diary will be used  
91      for the motivational follow-up calls made by the physiotherapist at 1, 2 and 4 weeks. After the 8  
92      weeks program is finished, the patient brings the diary to the hospital at the subsequent follow-up  
93      test. Patients in the intervention group are scheduled for physical tests and completion of  
94      questionnaires at 8 weeks and 6 months like the control group.

95

96 **Analysis and evaluation:** For the primary outcome, ISWT, parametrical statistics are used to  
97 describe and analyse data, if data are normally distributed. For the secondary outcomes, PEmbQoL  
98 and EQ-5D, data are on an ordinal scale, and hence data are described and analyzed using non-  
99 parametric statistics. Sick leave (number of days) are described and analyzed using parametrical  
100 statistics if data are normally distributed. For the evaluation of psychoactive drugs the chi2 test is  
101 used. The power calculation is based on the ISWT. The smallest clinical relevant difference has  
102 been reported to be between 50 m. (COPD rehabilitation) and 70 m. (cardiac rehabilitation). As a  
103 clinically relevant difference has not been investigated for LE patients and arbitrarily clinically  
104 relevant difference of 60 meters was decided upon. With a power of 80% and a significance level of  
105 5% a sample size of 60 patients is needed for each group. With an expected drop-out rate of 10% in  
106 each group we aim to include 140 patients in total.  
107

Effekten af et 8-ugers træningsforløb  
på fysisk kapacitet og livskvalitet  
hos patienter med lunge-emboli.  
En klinisk randomiseret undersøgelse

Projektgruppe:

[name], fysioterapeut

[name], sygeplejerske

[name], overlæge, dr. med.

[name], ledende terapeut

[name], forskningsansvarlig terapeut, ph.d.

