**Analyse og evaluering:** For det primære outcome, ISWT, anvendes parametrisk statistik til at beskrive og analysere data, såfremt data er normalt-fordelte. For de sekundære outcome, PEmb-QoL og EQ-5D, er der tale om ordinale data, og data beskrives og analyseres derfor med non-parametrisk statistik. Sygefravær (antal dage) beskrives og analyseres ved hjælp af parametrisk statistik, såfremt data er normalt-fordelt. Til evaluering af forbrug af psykofarmaka anvendes chi2 test. Power beregningen baseres på det ISWT. Den mindste klinisk relevante forskel er angivet til at være mellem 50 m. (KOL-rehabilitering) og 70 m. (hjerterehabilitering). Da en klinisk relevant forskel ikke er undersøgt for LE patienter valgtes en arbitrært sat klinisk relevant forskel på 60 m. Med en power på 80 % og signifikansniveauet sat til 5 % kræves en stikprøvestørrelse på 60 deltagere i hver gruppe. Med et forventet frafald på 10 % i hver gruppe sigtes der således mod at inkludere i alt 140 patienter.

**Etik:** Patienterne informeres mundtligt og skriftligt om undersøgelsens formål, og der indhentes skriftligt samtykke hos de deltagende patienter til at anvende deres data. Patienterne informeres om, at det er frivilligt at deltage, og at de til enhver tid har ret til at trække deres samtykke tilbage. Studiet er anmeldt til Region Midts paraplyanmeldelse til Datatilsynet den 26/08/2015 (godkendelse afventes), samt til Videnskabs Etisk Komité for Region Midtjylland (godkendelse afventes).

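### The primary outcome is fixed as ISWT change with an unspecified parametric analysis, and the protocol does not commit to adjusting for baseline ISWT or hospital, so an unadjusted comparison would lose precision.

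*Protocol*

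**What the plan says.** The Outcomes section of the protocol gives the endpoint as "Primary outcome: Change in physical capacity, measured with the Incremental Shuttle Walk Test (appendix 3) from baseline to 6 months follow-up". The same test is also done earlier: "an intermediary measurement is performed 8 weeks after baseline".

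On method, the Analysis and evaluation section says "For the primary outcome, ISWT, parametrical statistics are used to" describe and analyse the data, on condition that they are normally distributed. The Danish text, under Analyse og evaluering, says the same: "For det primære outcome, ISWT, anvendes parametrisk statistik til at beskrive og analysere data, såfremt data er normalt-fordelte". Across all outcomes that section chooses methods by measurement scale and distribution. Neither language version names a test or model for the ISWT, and neither mentions a covariate or a term for hospital.

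On allocation, Design and recruiting says "Block randomization by hospital is used to ensure that approximately an equal number of patients at each hospital will be allocated" to the two groups. Both versions list five hospitals.

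On sample size, a clinically "relevant difference of 60 meters was decided upon". The Danish text adds "Med en power på 80 % og signifikansniveauet sat til 5 % kræves en stikprøvestørrelse på 60 deltagere i hver gruppe". The paragraph goes on "With an expected drop-out rate of 10% in" each group, to reach 140 in total. It states no SD, no baseline-to-follow-up correlation and no sidedness.

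**The concern.** Every patient has a baseline ISWT before randomisation, and hospital is known for everyone. Both can be used in the analysis at no cost. A change score uses baseline in one fixed way: it subtracts the whole baseline value, as if the slope of the 6-month value on baseline were 1. When the slope is below 1, as it is for any correlation below 1 with equal variances, this over-corrects. The comparison then carries extra noise, and any chance baseline difference moves the estimate in the opposite direction. The baseline test is done by the physiotherapist at the outpatient visit and the follow-up tests by a blinded project physiotherapist. If testers differ, rho would be lower, which is where a change score loses most. The documents do not quantify this.

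Blocking by hospital balances the arms within hospitals. That balance reduces the true variance of the treatment comparison, but an analysis without hospital does not credit the reduction and reports a standard error that is somewhat too large.

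At stake are the width of the primary confidence interval and several points of power. The sentence is also open enough for the choice between adjusted and unadjusted analysis to be made after the data are seen.

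**Working it through.** **Inputs from the protocol:** difference 60 m, power 80%, significance level 5%, 60 per group, drop-out 10%, target 70 per group.

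**Assumed, because not stated:** a two-sided test, equal ISWT variance at baseline and 6 months, rho from 0.5 to 0.9, and a hospital share of variance of 5% to 10%.

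**Step 1: the plan's own figure.** The 60 per group cannot be reproduced directly without an SD, so solve for it. From n = 2·SD²·(1.960 + 0.842)²/60² with n = 60:

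SD = 60/2.802 × √(60/2) = 117.3 m

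(A one-sided test would imply about 132 m.) For drop-out, 60/0.9 = 66.7, so 67 per group or 134 in total. The target of 140 leaves 70 × 0.9 = 63 completers per group, so it is not short.

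**Step 2: baseline adjustment.** With common SD σ at both visits:

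- variance of change = 2σ²(1 − rho)
- residual variance after adjusting for baseline = σ²(1 − rho²)
- ratio f = (1 + rho)/2

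Take 117.3 m as the SD of change. Power at 60 per group is then Φ(2.802/√f − 1.960), and the n per group needed for 80% power is 60·f.

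| rho (assumed) | f | power at 60 per group | n per group for 80% |
|---|---|---|---|
| unadjusted change | 1 | 80% | 60 |
| 0.5 | 0.75 | 90% | 45 |
| 0.7 | 0.85 | 86% | 51 |
| 0.8 | 0.90 | 84% | 54 |
| 0.9 | 0.95 | 82% | 57 |

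**Step 3: chance baseline imbalance.** A baseline difference d between arms shifts the expected change-score difference by (1 − rho)·d, against the arm that started higher. With the SD of change held at 117.3 m, σ = 117.3/√(2(1 − rho)).

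- rho 0.5: σ = 117.3 m; one SE of the baseline difference = 117.3 × √(2/60) = 21.4 m; shift = 0.5 × 21.4 ≈ 11 m.
- rho 0.7: σ = 117.3/√0.6 = 151 m; one SE = 151 × √(2/60) = 27.6 m; shift = 0.3 × 27.6 ≈ 8 m.

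**Step 4: hospital.** Let hospital explain a share h of the variance of the analysed outcome. With allocation balanced within hospital, the true variance of the comparison is (1 − h) times the one the unadjusted test uses.

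- True two-sided alpha = 2·[1 − Φ(1.960/√(1 − h))]: 4.4% at h = 5%, 3.9% at h = 10%.
- Power with hospital in the model = Φ(2.802/√(1 − h) − 1.960): 82% and 84%.
- Power of the unadjusted test in the same setting = Φ(0.842/√(1 − h)): about 80.6% and 81.2%. The actual gain is therefore roughly 1 to 3 points.

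**Step 5: is the change definition itself the obstacle?** No. Write the model as 6-month value = a + b·arm + c·baseline + error and subtract baseline from both sides: change = a + b·arm + (c − 1)·baseline + error. The treatment coefficient b is the same. The outcome definition can stay, provided baseline is in the model.

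**The case against.** The strongest objection is that the protocol never says the comparison is unadjusted. A reader might infer from the change-score endpoint that the analysis is a t-test that ignores baseline and hospital. The documents do not support that: ANCOVA and mixed models are parametric too, and a change outcome can be analysed with baseline as a covariate. The exact model is also commonly left to an SAP, and none is at hand. This stands, and limits the point to a missing commitment with a conditional loss. It does not remove the point, because the protocol's own analysis section does fix how methods are chosen, by scale and normality alone. Followed literally, that leads most naturally to a simple two-group comparison.

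The objection on magnitude also stands in part. Neither rho nor the hospital share is in the documents. Nor does the protocol say whether its SD refers to change or to a single ISWT. If 117 m is the single-visit SD, an unadjusted change comparison already has about 95% power at rho 0.7 and 99% at rho 0.8, and the extra power from adjustment has little practical effect there. The variance ratio (1+rho)/2 is the same under either reading.

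Two further inferences should be resisted. The first is that leaving out hospital invalidates the test: it makes it slightly conservative. A change score also already removes stable differences in walking level between hospitals, so h would have to be variance in change, for which there is no evidence here. The second is that most drop-outs will have an 8-week test: nothing says when patients are expected to leave. A linear model on the 6-month value loses the same patients as a change score, and the recruitment target already allows for the expected loss.

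**Conclusion.** The point holds in a limited form. The protocol ties the primary endpoint to a change score, leaves the parametric method open, and does not commit to using two covariates it already has, one of which defines the randomisation blocks. If that becomes an unadjusted comparison, precision is lost at every rho below 1 under equal variances: 25% of the variance at rho 0.5, falling to 5% at rho 0.9. The corresponding power figures (90% down to 82%, against 80%) require the implied 117 m to be the SD of change and the test to be two-sided. A one-SE baseline imbalance would move the estimate by about 8 to 11 m at rho 0.7 to 0.5, against a target of 60 m. The hospital term is the smaller part, a matter of mild conservatism. Nothing here makes the planned analysis biased on average or the target of 140 inadequate. It is worth changing because the better method is free and because naming it in advance closes the choice of model.

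**What to change.** Replace the ISWT analysis sentence with one that names the model, for example: the primary analysis is a linear model for 6-month ISWT (or, equivalently, change in ISWT) in all randomised patients as allocated, with treatment arm, baseline ISWT and hospital as terms, reporting the adjusted mean difference in metres with its 95% CI.

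Optionally, fit it as a mixed model on the 8-week and 6-month ISWT with the same covariates, keeping the 6-month contrast as primary. Any drop-outs who have an 8-week test then contribute, under a missing-at-random assumption. The simpler linear model does not do this.

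The cost is one sentence. With five hospitals the covariates use five degrees of freedom (one for baseline, four for hospital), leaving 113 of 118 at 60 per group. No new data, visits or patients are needed, and the endpoint definition can stay as it is. The sentence should be in place before outcome data are examined by arm.

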### **Metode:**

*Design og rekruttering:* Undersøgelsen er et randomiseret multicenter-studie med 6 måneders opfølgning, med deltagelse af Regionshospitalet Silkeborg, Viborg, Randers, Horsens og Herning. Det er planlagt at i alt 140 patienter med medicinsk behandlet LE skal indgå i studiet, 70 i hver gruppe (Figur 1). Inklusionskriterierne er som følger: 1) Objektivt verificeret akut lungeemboli (ICD10 I260 og ICD10 I269), inklusiv recidiv 2) Behandling med antikoagulerende medicin; 3) 18-70 år; 4) Taler og forstår dansk. Patienterne ekskluderes ved 1) Lungeemboli som bi-fund ved scanning foretaget pga. anden sygdom; 2) Svær co-morbiditet (fx svær hjertesygdom, svær kronisk obstruktiv lungelidelse, cancer, svær psykiatrisk sygdom som fx skizofreni eller depression). Sygeplejersker eller fysioterapeuter i hjerteteamet på det enkelte sygehus udfører dagligt screeningsprocedure i afdelingen med henblik på at rekruttere egnede patienter i henhold til ovenstående kriterier. På dagen for udskrivelse informeres egnede patienter om den i gangværende undersøgelse, og den skriftlige deltagerinformation udleveres (Bilag 1). Patienterne har ret til to dages betænkningstid, og de kontaktes herefter telefonisk med anmodning om deltagelse i projektet. Ved accept af deltagelse indhentes skriftligt samtykke (Bilag 2) i forbindelse med patientens baseline test ved deres første besøg i AK-klinikken ca. 14 dage efter udskrivelsen. Efter baseline testen er udført, randomiseres patienterne til kontrol- eller forsøgsgruppe ved hjælp af uigennemsigtige kuverter. Der anvendes blokrandomisering på hospitalsbasis, for at sikre at ca. lige mange patienter på hvert hospital randomiseres til henholdsvis kontrol- og forsøgsgruppe

Figur 1. Flowdiagram.

[figure not shown]

*Effektmål og målemetoder:* Der videregives oplysninger fra patientens journal om alder, køn, BMI, medicinsk behandling af LE og diagnose (årsag til LE) ved baseline.

- Primære effektmål: Ændring i fysisk kapacitet, målt med Incremental Shuttle Walk Test (Bilag 3), fra baseline til 6 måneders follow-up.
- Sekundære effektmål: Ændring fra baseline til 6 måneders follow-up på følgende parametre:
  - Sygdomsspecifik livskvalitet målt med Pulmonary Embolism Quality-of-Life questionnaire
  - Generisk livskvalitet målt med EuroQol-5 Dimensions
  - Sygefravær (antal dage i de sidste 4 uger)
  - Forbrug af smertestillende medicin og psykofarmaka (i de sidste 4 uger).

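### Sick leave has no defined in-work population and is scored as change from a window containing the admission: this costs precision and clarity but does not bias the comparison

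*Protocol*

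**What the plan says.** In the Protocol's English Methods, under the outcomes heading, sick leave appears as "Sick leave (number of days in the past 4 weeks". The line above the list fixes its form: "Secondary outcomes: Change from baseline to 6 months follow-up on the following parameters". The Danish Metode section defines it in the same way.

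- **Who is asked.** The translation admits patients "18–80 years of age"; the Danish text has "3) 18-70 år; 4) Taler og forstår dansk". Neither version has an employment criterion.
- **What they can answer.** The translation offers none, 1 to 4, or 5 to 7 days per week. The Danish text offers none, fewer than 5, fewer than 10, or 10 or more working days over the four weeks. Neither list includes an answer for people without a job. The questionnaire itself is appendix 4, which is not shown.
- **When baseline falls.** Consent is taken "when the patients arrive for their baseline test in the AK-clinic (anti-coagulation clinic) app. 14 days after discharge", and randomization follows the baseline tests. On the stay itself, the usual-care paragraph says "A usual course of treatment typically entails 3-5 days of hospitalization where" anticoagulation is started.
- **How it is analysed.** The analysis paragraph applies parametric methods to the number of days if it is normally distributed. It names no subset of patients in work.

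**The concern.** Two features make this outcome hard to use.

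First, a retired or otherwise non-working patient has no sick leave to report. If that patient answers zero, the answer cannot be told apart from that of a worker with no absence; if the item is left blank, it cannot be told apart from missing data. Zeros that no treatment can alter pull the arm means together. If employment is never recorded, a later analysis plan cannot separate these patients from the answers alone.

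Second, the baseline recall period covers the embolism and its aftermath, so for a working patient it mostly records the acute event, not usual sick leave. A fall by 6 months is then expected with or without exercise.

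At stake are the precision and readability of one secondary outcome.

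**Working it through.** **The plan's own figure.** There is none to reproduce. The protocol's sample size concerns the walking test; no effect, standard deviation or power is given for sick leave.

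**1. The baseline window.** Inputs from the protocol: 28 days of recall, about 14 days since discharge, a typical stay of 3–5 days.

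- Admission plus convalescence: 14 + 3 = 17 to 14 + 5 = 19 days, or 17/28 = 61% to 19/28 = 68%.
- Before admission: 28 − 17 = 11 to 28 − 19 = 9 days.
- In working days: 17 × 5/7 ≈ 12 to 19 × 5/7 ≈ 14 of 20.

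On these timings the window always contains the admission.

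**2. Zeros from patients not in work.** Let p be the share not in work and scored zero. Among workers let the mean be μ, the standard deviation σ, CV = σ/μ, and the true difference d.

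- Whole-sample difference: (1 − p)d.
- Whole-sample variance: (1 − p)(σ² + pμ²).
- Information relative to workers only: σ²/(σ² + pμ²) = 1/(1 + p/CV²).

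The documents give neither p nor CV, so both are assumed:

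| | p = 0.3 | p = 0.4 |
|---|---|---|
| Difference retained, 1 − p | 70% | 60% |
| Information lost, CV = 2 | 0.075/1.075 = 7% | 0.10/1.10 = 9% |
| Information lost, CV = 1 | 0.3/1.3 = 23% | 0.4/1.4 = 29% |
| Information lost, CV = 0.5 | 1.2/2.2 = 55% | 1.6/2.6 = 62% |

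**3. How the two features combine.** For a change score, μ is the mean change, so a large common fall makes the absolute CV small. Illustration on assumed values: mean change of 10 days among workers, σ = 6, d = 3, 60 per arm, half in work.

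- Everyone: difference 1.5; SD = √(0.5 × 36 + 0.25 × 100) = 6.56; SE = 6.56 × √(2/60) = 1.20; power 24%.
- Workers only (30 per arm): SE = 6 × √(2/30) = 1.55; power 49%.

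If the mean among workers is near zero, the loss vanishes: at μ = 0 both analyses have 49% power. The zeros cost power only in combination with a non-zero mean.

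**4. Is the between-arm comparison biased?** No. Both arms share the same window, measured before allocation. In 20,000 simulated trials (60 per arm; half in work; assumed means among workers of 12 days at baseline and 4 against 2 days at 6 months), the control arm changed by −4.0 days with no treatment. The between-arm difference was −0.98 days both for change and for the 6-month value. The standard error was 1.05 for change and 0.49 for the 6-month value. That doubling depends on the assumed values, including no correlation between baseline and follow-up among workers.

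**5. When does change add noise?** With equal variances and correlation ρ, variances relative to the unadjusted 6-month value are:

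| ρ | Change, 2(1 − ρ) | 6-month value, adjusted for baseline, 1 − ρ² |
|---|---|---|
| 0.2 | 1.60 | 0.96 |
| 0.5 | 1.00 | 0.75 |
| 0.8 | 0.40 | 0.36 |

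Change is noisier than the plain 6-month value when ρ is below 0.5. The adjusted comparison is at least as precise as either.

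**The case against.** A reader might infer that, because the change is dominated by recovery from the admission, the sick-leave result is largely an artefact. The documents do not support this for the trial's comparison: the common fall cancels between arms, and the protocol plans no within-arm inference. The inference holds only for a within-arm change, should one be reported as an effect.

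A reader might also take it as stated that non-workers are counted as zeros. It is not. The protocol only summarises the answers, appendix 4 may contain an employment question, and an analysis plan could name a working subset. The list of data drawn from medical records does not settle this, since employment could sit in the questionnaire. What stands is that the protocol's own text fixes change from baseline, names no population for the outcome and lists no answer for people without a job.

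Nor does a non-worker appear as a perfect return to work under the planned score: zero at both visits is a change of zero. Confusion with full attendance arises on the 6-month value, which is why a switch to that value must come with the restriction to workers.

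An average over all randomized patients is also a legitimate quantity. It answers a different question, and the protocol does not say that it is the one intended.

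Finally, the size is not a figure for this trial. The formula treats sick leave as a count of days, whereas answers are collected in categories. The Danish upper age of 70 would probably admit fewer retired patients than the translation's 80.

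**Conclusion.** The point holds as a minor one. On the protocol's text, sick leave has no defined in-work population, and its baseline mainly records the acute event (17–19 of 28 days, given the typical stay and the approximate visit date).

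If patients without work are scored zero, the mean difference shrinks to 60–70% of its value among workers for an assumed non-working share of 0.3–0.4. The information loss then ranges from 7% to 62% over CVs from 2 to 0.5. That width reflects how little the documents fix, and no single value in it should be quoted as the loss in this trial.

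The randomized comparison is not biased. The cost is possible extra noise when baseline and follow-up are weakly correlated, and a within-arm fall that must not be read as an effect. The primary outcome and the stated sample size are untouched.

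**What to change.** Unless appendix 4 already does so:

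1. Record employment status before the embolism, and add a not-in-work answer to the sick-leave item at each visit.
2. State that sick leave is analysed in patients who were in work before the embolism. This is fixed before randomization, so the restriction keeps the randomized comparison.
3. Compare the arms on the 6-month value with baseline as a covariate, in place of change from baseline. Present any within-arm change as descriptive only.

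The cost is one questionnaire item, a sentence or two of analysis text, and a smaller denominator for one secondary outcome. With 60 evaluable patients per arm and an assumed non-working share of 0.3 or 0.4, 60 × 0.7 = 42 or 60 × 0.6 = 36 per arm would remain. Under the structural-zero model above, the patients left out carry no information on the effect.
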